### Sample size calculations

Household sample size calculations are based on an endline comparison of two groups (intervention versus control), using the proportion of women giving birth in a health facility as the primary outcome. On the basis of an observed institutional delivery rate of 50 % at baseline [10] and an assumed coefficient of variation of 0.2, a sample size of 60 intervention and 60 control clusters with a total of 20 women in each cluster are estimated to provide 80 % power to detect an 8 percentage point increase in the rate of institutional deliveries in the intervention group compared with the control at 5 % level of significance. Assuming a coefficient of variation of 0.1 reduces the detectable difference to 6 percentage points. It is anticipated that the study will have power to detect smaller differences once the analysis controls for covariates and utilises data from two survey rounds.

### Empirical analysis

The impact evaluation relies primarily on the household data. We use a difference-in-difference strategy to estimate impacts [34]. This involves a comparison of changes in the outcomes over time between the intervention and the comparison groups. The analysis exploits the longitudinal nature of the data generated by the recall period used in the two rounds of the household survey and information on the precise timing of the introduction of social franchising in each study area. Specifically, using individual level data, we regress each outcome on a dummy variable indicating whether social franchising has been introduced in the area at the time of birth, area fixed effects and quarter year fixed effects. Unadjusted estimates are reported as well as those that adjust for household characteristics. Controls for household characteristics include below the poverty line status, urban residence, religion, ethnicity, maternal education, parity, multiple birth and the recall period. We cluster the standard errors at the area level.

We test whether the social franchising model has an effect in two ways: the first analysis compares intervention areas with the two sets of comparison areas pooled together, and the second analysis compares the intervention areas with the comparison areas in adjoining districts without social franchising. The latter may arguably be less prone to selection bias since comparison areas in neighbouring districts are beyond the geographical reach of the project and may offer a more credible counterfactual. If the social franchising model is found to have an effect on any of the main outcomes, we conduct subgroup analyses with respect to below the poverty line status, maternal education and caste. Finally, to assess the so-called parallel trends assumption that underpins the difference-in-difference approach, we exploit the recall period in the household data to verify that trends in each of the outcomes are similar between the three study arms before the introduction of the social franchising model. Evidence of diverging pre-trends would be a cause for concern. Baseline outcomes and characteristics of women are also summarised for each study arm with continuous variables presented as mean (standard deviation) and categorical variables by frequencies (percentage). An additional file describes the empirical strategy of the impact evaluation in further detail [see Additional file 4].

The presence of multiple outcomes leads to the risk of arbitrarily selecting statistically significant outcomes where high values of test statistics arise by chance. Testing each hypothesis one at a time with a fixed significance increases the probability of a type-I error exponentially as the number of outcomes tested grows. We deal with multiple outcomes using several procedures that are implemented for conceptually similar groups of outcomes listed in Tables 2, 3 and 4 [35, 36]. First, we present standardised treatment effects by creating an index for multiple outcomes within each domain and testing for an effect on the index. Implicitly, this weighs each outcome the same within a domain. Second, we present family-wise *p* values adjusted to account for the multiple outcomes within a domain using the free step-down resampling method of Westfall and Young [37].

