### Data collection

The evaluation relies primarily on several tools that are administered over two rounds of data collection: a household survey of women who recently gave birth and a health provider survey. The first round of data collection was in January 2015, and the second round is planned for March 2016. This means the impact of the social franchise intervention is assessed approximately 2 years after its start. Information on the precise timing of the introduction of social franchising in each cluster is based on administrative data provided by the franchisor triangulated with responses to the health provider survey. It is worth noting that the research outlined in this protocol is closely coordinated with several other data collection activities—direct observations of births and a case study of three social franchise models that will provide additional insights.

The household survey is administered to women as a cross-section at two points in time and serves as the main source of data on our study outcomes. Eligible respondents include all women who gave birth in the previous 24 months (first round) or 18 months (second round), including those who had a stillbirth or whose child died since birth. Eligible women are identified through a census of households, conducted 1 month before the household survey. Every member of the household is listed and then, for women aged 15 to 49 years, a series of questions probe whether she gave birth to a baby that was born alive, born dead or lost before birth. Using this sampling frame, a maximum of 23 eligible women in each cluster are randomly selected for interview. The household survey tool includes the following modules: (1) household listing, (2) general healthcare interactions, (3) household characteristics, (4) wellbeing of husband, (5) pregnancy history, (6) family planning and antenatal care, (7) delivery and postnatal care, (8) child health, (9) interactions with community health workers, (10) information and perceptions of healthcare, and (11) wellbeing, mental health and physical health.

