### Outcomes

The impact of the social franchise model is assessed using a comprehensive set of pre-specified outcomes that are measured using the household data. An extensive list of outcomes, 59 indicators in total, is shown in Tables 2, 3 and 4. They cover the continuum of care from antenatal care through postnatal family planning and include various types of indicators including healthcare utilisation, process of care, healthy behaviour, patient experience, patient information and financial strain. The study outcomes are organised according to conceptually similar groups that are required when implementing methods to deal with many outcomes.

**Table 2 Tab2:** Antenatal outcomes of the impact evaluation by domain

Indicator	Type of indicator
1. ANC utilisation	
Received at least three ANC visits (%)	Use of healthcare
Received ANC visit in first trimester (%)	Use of healthcare
Number of ANC consultations (visits)	Use of healthcare
Received visit from ASHA during pregnancy (%)	Use of healthcare
2. ANC content of care	
Fully immunised with tetanus toxoid (%)	Process of care
Received iron supplementation during pregnancy (%)	Process of care
Took iron supplementation during pregnancy for at least 100 days (%)	Process of care
Received test results for syphilis received (%)	Process of care
Abdominal examination during ANC (%)	Process of care
Received a drug for intestinal worms during pregnancy (%)	Process of care
Received a drug to prevent malaria (%)	Process of care
Multiple birth pregnancy detected during ANC (%)	Process of care
ANC content of care score of six items (index 0 to 1)	Process of care
3. ANC knowledge and preparedness	
Mother knowledge of pregnancy complications (index 0 to 1)	Patient knowledge
Mother knowledge of signs of delivery complications (index 0 to 1)	Patient knowledge
Birth preparedness (financial, transport, blood donor, attendant, safe delivery kit) (index 0 to 1)	Healthy behaviour

**Table 3 Tab3:** Intrapartum care outcomes of the impact evaluation by domain

Indicator	Type of indicator
1. Delivery care utilisation	
Gave birth in a health facility (%)	Use of healthcare
Gave birth with a doctor, nurse or midwife (%)	Use of healthcare
Had a caesarean section (%)	Use of healthcare
2. Recommended delivery care practices	
Delivery attendant used gloves (%)	Process of care
Delivery attendant washed hands with soap (%)	Process of care
Woman had her BP measured (%)	Process of care
Mobility during labour (%)	Process of care

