Oral fluids during labour (%)	Process of care
Heart rate of baby monitored with intermittent or continuous auscultation (%)	Process of care
Use of anti-shock garment (%)	Process of care
3. Harmful or ineffective delivery care practices	
Shaving pubic hair (%)	Process of care
Enema given (%)	Process of care
Lithotomy position during labour (%)	Process of care
Intravenous fluids during labour (%)	Process of care
4. Delivery care practices frequently over used	
Urinary catheter (%)	Process of care
Pain control by epidural analgesia (%)	Process of care
Oxytocin augmentation (%)	Process of care
Episiotomy (%)	Process of care
5. Disrespect and abuse	
Support during labour (%)	Patient experience
Medical procedure performed without consent (%)	Patient experience
Shouted, scolded or humiliated by health worker (%)	Patient experience
Slapped, pinched or hit by health worker (%)	Patient experience
Gave birth with privacy (%)	Patient experience
Refused care for inability to pay (%)	Patient experience
Kept in facility for inability to pay (%)	Patient experience
Felt disrespected or abused during facility stay (%)	Patient experience
6. Economic consequences	
Out-of-pocket spending on delivery care (NRS)	Financial strain
Borrowed money to pay for delivery care (%)	Financial strain
Household in debt to pay for delivery care (%)	Financial strain
Received JSY cash incentive (%)	Financial strain

**Table 4 Tab4:** Postpartum and newborn outcomes of the impact evaluation by domain

Indicator	Type of indicator
1. Postpartum care	
Received postpartum care within 48 h of birth (%)	Use of healthcare
Newborn received postnatal care within 48 h of birth (%)	Use of healthcare
2. Newborn content of care	
Clean cord care (clean instrument to cut and tie the cord, and nothing put on cord) (%)	Process of care
Thermal care (immediate drying, wrapping, skin to skin and delayed bathing) (%)	Process of care
Baby weighed at birth (%)	Process of care
Baby registered and received certificate (%)	Process of care
3. Neonatal health	
Neonatal mortality (per 1000 live births)	Health outcome
One-day mortality (per 1000 live births)	Health outcome
Birth weight (kg)	Health outcome
4. Breastfeeding	
Immediate breastfeeding within 1 h of birth (%)	Healthy behaviour
Colostrum given to baby (%)	Healthy behaviour
Exclusive breastfeeding for 3 days (%)	Healthy behaviour
5. Family planning	
Modern contraceptive use at 3 months postpartum (%)	Use of healthcare

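### Dating exposure at birth for every outcome misclassifies early antenatal care and shrinks antenatal effects; if knowledge is measured at interview, Group A has no pre-franchise value for it

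*Protocol article*

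**What the plan says.** The Empirical analysis section of the protocol article sets the regression: "we regress each outcome on a dummy variable indicating whether social franchising has been introduced in the area at the time of birth", with fixed effects for area and for calendar quarter. The rule covers each outcome, and the Outcomes section counts them: "An extensive list of outcomes, 59 indicators in total, is shown in Tables 2, 3 and 4". By table these are 16 antenatal, 30 intrapartum and 13 postpartum or newborn. No other exposure date is given for any of them.

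The outcomes refer to different times. Table 2 includes "Received ANC visit in first trimester", "Took iron supplementation during pregnancy for at least 100 days" and "Mother knowledge of pregnancy complications (index 0 to 1"). Table 4 includes "Modern contraceptive use at 3 months postpartum".

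On timing, the Data collection section says: "The first round of data collection was in January 2015, and the second round is planned for March 2016". Respondents are "all women who gave birth in the previous 24 months (first round) or 18 months (second round"). The Study design section says that Group A clusters already held a franchisee when selected, 14 months after the first providers were contracted. It takes their pre-franchise period from births recalled at round 1, and expects some Group B clusters to convert later. Additional file 4, cited for further detail on the empirical strategy, is not shown.

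**The concern.** A first trimester ends about 6 months before birth. A woman who delivers 4 months after the franchise opens could not have had a first-trimester visit under it, yet she counts as exposed for that outcome. If she delivers within about 3.3 months (100 days) of opening, she cannot have taken all 100 days of iron under it either. Women with no or partial exposure are averaged into the exposed group, which pulls antenatal effects towards zero.

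This matters because antenatal care is what the lower network tiers are paid for: SkyCare for antenatal referrals, SkyHealth for completing three consultations. Antenatal estimates also feed the domain indices and the cost-effectiveness model.

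Knowledge raises a different problem. Recall can place an antenatal visit in time, but it cannot recover what a mother knew before the franchise opened. If the items ask what she knows at interview, every Group A value was taken after introduction, including values from women whose births are coded unexposed.

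**Working it through.** **The plan's own figure.** The article gives no figure for this point. The 8 points used below as a yardstick come from its sample size for facility birth, which reproduces. Clusters per arm = 1 + (1.96 + 0.84)² × [(0.50×0.50 + 0.58×0.42)/20 + 0.2² × (0.50² + 0.58²)] / 0.08² = 1 + 7.849 × 0.04814 / 0.0064 = 60.03, against 60 stated. That outcome is correctly dated.

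**Inputs.** From the article: survey months, recall windows of 24 and 18 months, 60 clusters per group, 20 women per cluster per round, and first contracts 14 months before area selection. Assumed: births spread evenly over the windows (January 2013 to January 2015, and September 2014 to March 2016), start dates between November 2013 and January 2015, and no Group B conversion.

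**Step 1: births affected, per Group A cluster.** Births accrue at 20/24 per month in the round 1 window and 20/18 per month in the round 2 window.

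- Start November 2013: exposed births = 14 × 20/24 + 20 = 31.7. Within 6 months of introduction: 6 × 20/24 = 5.0, or 16%. Within 9 months: 7.5, or 24%.
- Start October 2014: exposed births = 3 × 20/24 + 17 × 20/18 = 21.4. Within 6 months: 2.5 + 6.67 = 9.17, or 43%. Within 9 months: 2.5 + 10.0 = 12.5, or 58%.

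So 16% to 43% of births coded exposed had the whole first trimester before the franchise, and 24% to 58% came from pregnancies begun before it.

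**Step 2: effect on the estimate.** The stated regression (at-birth dummy, area and quarter effects) was fitted to noiseless data with a true effect of 1, under two profiles:

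- Step: zero for births less than 6 months after introduction, 1 from then on (the first-trimester item).
- Ramp: months since introduction divided by 9, capped at 1 (share of pregnancy exposed).

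| Assumed starts | Comparison | Step | Ramp |
|---|---|---|---|
| All November 2013 | A vs C | 0.777 | 0.805 |
| All November 2013 | A vs B+C | 0.808 | 0.836 |
| Spread over 14 months | A vs C | 0.568 | 0.642 |
| Spread over 14 months | A vs B+C | 0.624 | 0.687 |

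For a true 8 points, the ramp gives 8 × 0.642 = 5.1 to 8 × 0.836 = 6.7. The step gives 8 × 0.568 = 4.5 to 8 × 0.808 = 6.5. Placing births continuously in time and adding a common January 2014 start moves the ranges only slightly, to 0.56–0.83 (step) and 0.67–0.87 (ramp). When the step effect is instead regressed on exposure dated to its own window, the coefficient is 1.00.

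**Step 3: knowledge.** Group A clusters had a franchisee at selection, before the January 2015 interviews. Exposure dated at interview is therefore 1 in both rounds for all 60. It does not vary within an area, and the area effects absorb it. Only a Group B cluster that converts between January 2015 and March 2016 moves from 0 to 1. The number of such clusters is not given.

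**The case against.** **Most antenatal items can respond late in pregnancy.** Only one of the 16 is tied to the first trimester. Number of visits, tetanus immunisation, abdominal examination and birth preparedness can all change after it. A woman who delivers 6 months after opening had two trimesters under the franchise. This stands, and it is why the ramp, not the step, is the fair model for most of Table 2.

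**A reader might infer that a null antenatal result could come from the coding alone.** The figures do not support that. Even the severe assumption of no effect on any birth within 9 months of introduction, with spread starts, leaves 41% of the effect (A vs C). That assumption is too strict even for the first-trimester item, because a visit in month 3 falls about 6 months before birth.

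**A reader might infer that the knowledge outcomes have no baseline at all.** That is too broad, because Group B converters would have a round 1 measure. It also depends on a questionnaire that is not shown: items asking what was known during pregnancy would be datable. Antenatal contact is one route to knowledge, and women who delivered before introduction missed it. Advertising and community messages could still reach them, so contamination is plausible but its size is unknown.

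**Contraception at 3 months postpartum might look misdated in the other direction.** The programme includes postpartum counselling and postpartum intrauterine devices, so birth is a defensible anchor.

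**Additional file 4 may set outcome-specific dates.** If it does, the article's sentence still needs to be brought into line with it.

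**Conclusion.** The point holds for antenatal outcomes in pregnancies that span the introduction date. Followed as written, the rule biases these effects towards zero and costs power. The estimate keeps about 57% to 81% of a true first-trimester effect and about 64% to 84% of one that rises with the share of pregnancy exposed. Late-pregnancy items are affected less than first-trimester ones. The direction follows from the rule; the sizes rest on assumed start dates, evenly spread births and the two effect profiles.

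The knowledge point holds for Group A, on condition that the items measure knowledge at interview. Adjusting for recall period, as the plan does, repairs neither problem. Facility birth and the other intrapartum, newborn and breastfeeding outcomes are unaffected.

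**What to change.** - **Antenatal outcomes:** replace the at-birth dummy with exposure dated to the outcome window. Use franchise present by the end of the first trimester for the first-trimester item, and share of pregnancy exposed for the others. Add a sensitivity analysis that excludes births in the 9 months after introduction.
- **Knowledge indices:** state when the knowledge refers to. If it is knowledge at interview, date exposure at interview and say that the difference-in-difference is identified only from Group B clusters that convert between rounds. Otherwise report a post-exposure comparison and do not call it a difference-in-difference.
- **All other outcomes:** keep the at-birth rule. Dating contraception at 3 months postpartum is an optional sensitivity analysis.

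The cost is some recoding and a short paragraph of analysis text. Birth dates and introduction dates are already part of the planned analysis, so no new data are needed. The sensitivity analysis would lose about 24% to 58% of exposed Group A births for antenatal outcomes, depending on start dates. That is why exclusion should not be the main analysis.

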## Abstract

**Background:**

Social franchising is the fastest growing market-based approach to organising and improving the quality of care in the private sector of low- and middle-income countries, but there is limited evidence on its impact and cost-effectiveness. The “Sky” social franchise model was introduced in the Indian state of Uttar Pradesh in late 2013.

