**Fig. 1 Fig1:**
[figure not shown]
Study design and data collection

The selection of study areas was done 14 months after the first health providers were contracted at which time there were 50 SkyHealth and 343 SkyCare providers in the social franchise network. The selection of study clusters proceeds according to the following steps. First, we link every social franchisee to the census area in which it is located and select, at random, 60 intervention clusters (Group A). Second, we select similar controls by matching without replacement the intervention clusters to 60 comparison areas within the same three districts (Group B) [27]. As can be seen in Fig. 2, we impose a buffer zone of 0.5 km around intervention clusters to limit problems of contamination. We perform exact matching on district and urban residences and then within each strata, select pairs of clusters (nearest neighbour) with the smallest distance based on a Mahalanobis metric that is computed using census data on total population, % under 6 years, % females under 6 years, % literate females, % scheduled tribe, % scheduled caste, % cultivator and % “other” workers. Finally, we perform the same matching procedure to select 60 comparison areas in neighbouring districts (Group C).

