**Fig. 2 Fig2:**
[figure not shown]
Map of study clusters in the three intervention districts

The selection of study clusters provides variation in the social franchise that facilitates identification of its impact. Variation over time is generated in two ways. The 2-year recall period of the household survey means that we have almost 12 months of baseline data even in areas where social franchising is introduced. Moreover, we anticipate that over time, some of the Group B study clusters will become intervention areas as the social franchise network expands generating further variation over time. Geographical variation in the placement of the social franchise is generated by our selection of comparison areas.

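### The pre-trend check cannot verify parallel trends: with about 10 to 12 months of common pre-period births it has roughly 7-9% power against a divergence that would bias facility birth by the full 8-point target effect

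*Protocol article*

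**What the plan says.** The Empirical analysis section regresses each outcome on a dummy for franchising having been introduced by the time of birth, with area and quarter-year fixed effects. To examine the parallel-trends assumption, it will use recall data to "verify that trends in each of the outcomes are similar between the three study arms before the introduction of the social franchising model". It adds: "Evidence of diverging pre-trends would be a cause for concern". Further detail on the empirical strategy is deferred to Additional file 4, which is not shown.

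The length of the pre-period follows from four statements:

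- The abstract says the franchise "was introduced in the Indian state of Uttar Pradesh in late 2013".
- Study design: "The selection of study areas was done 14 months after the first health providers were contracted". It also says that "we have almost 12 months of baseline data even in areas where social franchising is introduced".
- Data collection: "The first round of data collection was in January 2015, and the second round is planned for March 2016".
- Data collection also sets the recall windows, at 24 months in round 1 and 18 months in round 2.

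The only power calculation, in Sample size calculations, is for an endline two-group comparison of facility birth.

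**The concern.** Franchise placement is not randomised, and the Discussion acknowledges the bias this may cause. The effect estimate is causal only if intervention and comparison areas would otherwise have moved in parallel. The pre-trend check is the one place where the data speak to that assumption.

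A slope estimated over less than a year of births is imprecise. The bias from a diverging trend, however, accumulates over the longer distance between the pre- and post-introduction births. A divergence too small to see in the pre-period could therefore create or cancel an effect of the size the study is looking for. If the absence of visible divergence is then reported as verification, readers will place more trust in the causal claim than the data can support.

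**Working it through.** **1. The plan's own figure.** Inputs from Sample size calculations: rates of 50% and 58%, m = 20 women per cluster, coefficient of variation k = 0.2, 80% power, 5% level (taken as two-sided).

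c = 1 + (1.96 + 0.84)² × [p1(1−p1)/m + p2(1−p2)/m + k²(p1² + p2²)] / (p1 − p2)²

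The bracket is 0.0125 + 0.01218 + 0.02346 = 0.0481, which gives c = 60.03 clusters per arm. Power at 60 clusters is 79.98%. With k = 0.1 the detectable difference is 6.4 points, consistent with the stated 6. The plan's calculation reproduces, so the inputs are read correctly.

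**2. Length of the common pre-period.** Round 1 reaches back 24 months from January 2015. If areas were selected at about that time, the earliest areas have 24 − 14 = 10 months before introduction. The article's own figure is almost 12. Round 2 reaches back 18 months from March 2016, to about September 2014, so it adds no births before the late-2013 start. I use T = 10 and T = 12.

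**3. Precision of the slope difference.** Assume births are spread evenly over the recall window, the individual SD is 0.5 (50% rate), and slopes do not vary between clusters beyond sampling error.

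- Pre-period births per arm: n = 60 × 20 × T/24, which is 500 at T = 10 and 600 at T = 12.
- SE of the slope difference = 0.5 / √(n × T²/12) × √(1 + 1/number of comparison arms).

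**4. Slope that matters.** I simulated the article's fixed-effects model with births uniform in both recall windows. With introduction at month 12, each 1 point per month of linear divergence biases the impact estimate by about 19.5 points. The critical slope is therefore 8/19.5 = 0.41 points per month. With introduction at month 10 it is 0.42 to 0.44.

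**5. Power** = Φ(r − 1.96) + Φ(−r − 1.96), where r = 0.41/SE:

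| Pre-period | Contrast | SE (points/month) | 95% half-width | Power |
|---|---|---|---|---|
| 10 months | A vs C | 1.10 | 2.1 | 6.6% |
| 10 months | A vs B+C | 0.95 | 1.9 | 7.2% |
| 12 months | A vs C | 0.83 | 1.6 | 7.8% |
| 12 months | A vs B+C | 0.72 | 1.4 | 8.8% |

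Multiplied by 19.5 months, the half-widths correspond to about ±28 to ±42 points on the impact estimate.

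**6. Cross-check.** Taking both the SE and the bias from the simulated fixed-effects design gives 6.8% and 7.1% at 10 months, and 7.7% and 8.5% at 12 months (A vs C, then A vs B+C).

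**7. Sensitivity.**

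- Pre-to-post distance of 16 to 20 months: 6.5-10.7%.
- 23 women per cluster (the stated maximum), same distances: 6.8-11.5%.
- Entry of Group A clusters spread evenly over months 10 to 23 of the window (an assumption), using every cluster's own pre-introduction births: about 24-25%.
- A full 24-month pre-period everywhere: n = 1,200, SE 0.29 (A vs C) and 0.26 (A vs B+C), power 29% and 36% at 0.41 points per month.
- Any variation in slopes between clusters would lower all of these figures.

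**The case against.** **The article states no test.** A reader might infer that the plan takes a non-significant pre-trend difference as confirmation, or that it runs 59 tests at 5% and so expects about three false alarms. The text supports neither. It gives no significance level or pass/fail rule for pre-trends, and the sentence itself opens by saying the aim is to assess the assumption. Nor is it a fault that the article names no consequence beyond concern, because such detail may be in Additional file 4. All of this stands. It does not rescue the check, since imprecision belongs to the data: a graph or an interval carries the same ±1.4 to ±2.1 points per month against a critical slope of about 0.41.

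**Roll-out was probably staggered.** The 14 months run from the first contracts, and the analysis uses area-specific introduction dates, so later-joining clusters have longer pre-periods. This stands and is why 7-9% is not the only figure to quote. Entry dates are not given. Even spacing gives about 25%, still far below 80%.

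**The check still has some value.** A reader might conclude that it can show nothing. That goes too far, because a gross divergence could be detected.

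**There are other safeguards.** Clusters are matched on district, urban residence and census variables. A separate contrast uses only Group C, and the Discussion admits the selection problem. These make divergence less likely, but they do not make the check more informative about it.

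**Conclusion.** The point holds as one about precision. The design cannot verify similar pre-introduction trends to the accuracy that the impact estimate needs. For facility birth, power against a divergence worth the full 8-point target effect is about 7-9% with the common pre-period, about 25% under evenly staggered entry, and 29-36% with a full 24-month pre-period.

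These figures assume a 50% binary outcome, evenly spread births, a linear divergence that persists through follow-up, a two-sided 5% level and no extra variation in slopes between clusters. Other outcomes have other variances, so the percentages do not transfer directly. No reading of the roll-out examined here brings power near 80%. The plan should be changed, but the impact model itself is not shown to be wrong.

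**What to change.** - Replace *verify* with *assess* in Empirical analysis.
- Report the pre-period slope difference with its 95% confidence interval for facility birth and for each of the 14 domain indices (3 domains in Table 2, 6 in Table 3, 5 in Table 4), using cluster-specific introduction dates.
- Beside each main estimate, give the bias implied by that interval, or the break-even slope that would remove the effect. The multiplier (about 19.5 months under the assumptions here) should be recomputed from the actual birth and introduction dates by running the impact model on a pure group-by-time trend.
- State in advance that not detecting a difference is not evidence of parallel trends.
- Optionally, if the pregnancy-history module covers an outcome for earlier births, use it to lengthen the pre-period. The article names the module but does not show its content, so this cannot be relied on.

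The cost is analysis code and a few sentences, with no new data. The drawback is that the reported uncertainty around the main estimates will be visibly wider.
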